### Adverse Events

Any adverse effects observed or reported by patients will be documented and taken into consideration in the study’s results. In addition, these patients will be referred for medical care for proper treatment.

### Statistical Methodology

#### Sample Size Calculation

The G*Power 3.1 (Heinrich-Heine-Universität Düsseldorf) program was used to determine the sample size. The calculation was based on the HADS total score, which is defined as the primary outcome of the study, assuming a repeated-measures design with 3 groups (home-based, face-to-face, and control) and 3 assessment time points (baseline, postintervention, and 4-week follow-up). Considering an α level of .05 and power of .80, an effect size of *f* of 0.25 (moderate) was assumed for the group × time interaction, with an assumed correlation among repeated measures of 0.50 and a nonsphericity correction (ε) of 1.0. Under these assumptions, a sample of at least 42 participants, randomized into the 3 groups, is required. This sample size was calculated to detect differences between groups and was not designed to formally demonstrate equivalence between the interventions. Anticipating a dropout rate of approximately 30% (18/60), a total of 60 participants will be recruited to ensure the necessary final sample size of 42 participants.

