#### Statistical Analysis

The analysis will be conducted using the ITT principle, including all randomized participants. Per-protocol sensitivity analyses will also be performed. For continuous variables, a linear mixed model will be used, with fixed effects for group (face-to-face, home-based, and control), time (baseline, postintervention, and follow-up), and group × time interactions. Participants will be modeled as a random effect. Baseline values will be included as part of the repeated-measures structure rather than as covariates, allowing the estimation of within- and between-group changes over time. Age and sex will be considered as covariates in adjusted models if baseline imbalances or clinically relevant associations with the outcomes are identified. The home-based vs face-to-face comparison will be interpreted based on effect estimates and confidence intervals and will not be treated as a formal equivalence analysis. This model, which treats repeated within-participant measures as a random effect, will be used. An appropriate covariance structure for the repeated measures will be selected based on model fit criteria. This method allows for the management of missing data under the assumption that they are missing at random. In cases of systematic losses, multiple imputations may be used as a complementary analysis.

For categorical or dichotomous variables, the chi-square or Fisher exact tests will be applied, where appropriate. For all hypothesis tests, the α level for statistical significance will be set at *P*<.0, corresponding to a 95% confidence level. To assess the magnitude of significant differences between the preintervention and postintervention moments and between groups, the Hedge *g* (x ®1–x ®2⁄ SD grouped) will be calculated. The effect size magnitudes will be interpreted as follows: <0.2, no effect; 0.2 to 0.4, small; 0.5 to 0.7, moderate; and ≥0.8, large [58]. Secondary outcomes will be analyzed using the same modeling strategy; however, these analyses will be considered exploratory, and no formal adjustment for multiple comparisons is planned. The data will be analyzed using IBM SPSS software, version 20.0, licensed to UDESC, and Microsoft Office Excel for Windows.

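### The stated sample-size inputs give 36 participants, not 42; an input needs checking, and f = 0.25 should be translated into SD units

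*Protocol article*

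**What the plan says.** All quotes are from the protocol article. The Sample Size Calculation section bases the calculation on the HADS total score, "assuming a repeated-measures design with 3 groups (home-based, face-to-face, and control) and 3 assessment time points". The error rates are "Considering an α level of .05 and power of .80". The effect size f is given as "0.25 (moderate) was assumed for the group × time interaction", "with an assumed correlation among repeated measures of 0.50" and a nonsphericity correction of 1.0. The conclusion is: "Under these assumptions, a sample of at least 42 participants, randomized into the 3 groups, is required". Allowing for 30% dropout (18 of 60), the target becomes 60 recruited.

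The Statistical Analysis section gives bands for Hedges g, the standardised difference used to describe significant results: "0.5 to 0.7, moderate; and ≥0.8, large". Nowhere is f = 0.25 expressed in HADS points or as an SD difference between arms.

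**The concern.** The section states every input that the G*Power within-between interaction routine needs, so its result can be checked without further assumptions, apart from the effect-size option, for which the default is used here. The printed number does not come out. The paragraph then describes a calculation other than the one performed, and a reader cannot tell which input differs.

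The second issue is what the assumed effect means. A reader told that the trial has 80% power for a moderate effect may think of roughly half an SD between arms. On the interaction term, f = 0.25 is considerably larger than that under the patterns of means examined. This affects how a null result on the primary outcome would be read.

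**Working it through.** **Inputs.** From Sample Size Calculation: k = 3 groups, m = 3 measurements, f = 0.25, ρ = 0.50, ε = 1.0, α = .05, target power .80. From Randomization and Blinding: 1:1:1 allocation, so N rises in steps of 3.

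**Formula** (G*Power default metric, within-between interaction): λ = f²·N·m·ε/(1−ρ), df1 = (k−1)(m−1)ε, df2 = (N−k)(m−1)ε. Power is the upper tail of the noncentral F beyond the α critical value.

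**Attempt to reproduce 42 with the stated inputs (m = 3, df1 = 4):**

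| N | λ | df2 | Power |
|---|---|---|---|
| 33 | 0.0625·33·3/0.5 = 12.375 | 60 | 0.781 |
| 36 | 13.5 | 66 | 0.823 |
| 42 | 15.75 | 78 | 0.887 |
| 60 | 22.5 | 114 | 0.975 |

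The requirement is 36 (35 if arms may be unequal, power 0.809). Simulating the repeated-measures ANOVA gave 0.826 at 36 and 0.888 at 42, which confirms the formula.

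**What does give 42?** With m = 2 and all else unchanged (df1 = 2), N = 39 gives λ = 9.75 and power 0.769; N = 42 gives λ = 10.5 and power 0.803. Keeping m = 3 and changing one other input also makes 42 the minimum:
- ρ = 0.40: power 0.815
- ε = 0.75: power 0.806
- α = .025: power 0.820
- f = 0.23: power 0.822

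Other tests or effect-size options at the stated inputs do not give 42: within-factor test 30, between-factor test 108, 'as in SPSS' 102, 'as in Cohen' 99.

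**Dropout step.** 42/(1−0.30) = 60, as stated.

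**f on the SD scale.** This needs a pattern of means, which the article does not give. *Assumption:* both active arms change by d SD at post-intervention and at follow-up, and control does not change. The interaction residuals are −2d/9, d/9, d/9 in each active arm and 4d/9, −2d/9, −2d/9 in control. Their root mean square is 2d/9 = 0.2222d, so f = 0.25 means d = 0.25/0.2222 = 1.125. Other patterns tried give about 1.06 (two time points) to 1.5 SD.

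**Omnibus interaction power under that pattern (m = 3):**

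| d (SD) | f = 0.2222d | N = 42 | N = 60 |
|---|---|---|---|
| 0.5 | 0.111 | 0.24 | 0.34 |
| 0.7 | 0.156 | 0.45 | 0.63 |
| 0.8 | 0.178 | 0.57 | 0.76 |

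**Precision of home-based vs face-to-face.** At ρ = 0.5 the SD of change is √(2(1−0.5)) = 1 SD, so the standard error of a difference in change is √(2/n).
- n = 14 per arm: 0.378 × 2.056 (t, 26 df) gives a 95% CI half-width of ±0.78 SD.
- n = 20 per arm: 0.316 × 2.002 (t, 57 df, variance pooled over three arms) gives ±0.63 SD.

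**The case against.** **The count error is on the safe side.** This stands. Under the stated inputs 42 completers exceed the .80 target. A reader might infer that the wrong number leaves the trial underpowered, but the article's own inputs show the opposite. What remains is that the stated requirement does not follow from the stated inputs.

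**The two-time-point origin is not shown.** This also stands. It is tempting to say that 42 was computed for baseline and post-intervention only, because that gives 42 exactly. The article does not say so, and at least four other single changes also give 42.

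**Moderate refers to Cohen's f, not to Hedges g.** This is fair. An f of 0.25 is conventionally medium, and the article never says that its f label and its g bands are one scale. A reader might infer that the article contradicts itself by calling one effect both moderate and large. It does not, strictly: the link runs through an assumed pattern of means and G*Power's default metric. The practical point survives, because every pattern tried exceeds the 0.8 threshold.

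**The low power figures are for a 4-df omnibus test.** This is correct. Under the same pattern, a contrast of the pooled active arms with control, averaging both post-baseline visits, has power of about 0.41 (0.5 SD) and 0.68 (0.7 SD) at 42, and 0.55 and 0.83 at 60. The primary hypothesis in the Discussion is active versus control, but the sample size was set on the interaction and no such contrast is named.

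**The home-based vs face-to-face comparison is already qualified.** The article says that it is not an equivalence test and will be read from estimates and intervals, and it claims no power for it. Giving the expected interval width is therefore optional.

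**Conclusion.** The arithmetic point holds with no assumption beyond the printed inputs and G*Power's default effect-size option: they require 36, not 42, a gap of 6 participants, and 42 gives power of about 0.89. At least one printed input differs from the one used. Which one cannot be settled from the article; two measurements is plausible but unconfirmed. The error is conservative for the count, and 60 recruited remains adequate under the stated assumptions.

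The effect-size point is a needed clarification that rests on labelled assumptions. With equal, sustained improvement in both active arms and a flat control, f = 0.25 corresponds to about 1.1 SD in change, which falls in the large band of the Hedges g scale. For differences in the 0.5 to 0.7 SD band, omnibus power is about 0.24 to 0.45 at 42 and 0.34 to 0.63 at 60.

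**What to change.** Keep 60 recruited and check the saved G*Power run. Then do one of the following:
- If the stated inputs are the intended ones, restate the result: for 3 groups and 3 time points, 36 completers give 82% power and the 42 expected completers give about 89%.
- If another input was actually used, correct that input in the text and keep 42. Do not attribute 42 to two time points unless the run shows it.

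Add one sentence translating f = 0.25 into an SD difference in change (about 1.1 SD), with the pattern of means and the effect-size metric named as assumptions, and give the omnibus power for 0.5 to 0.7 SD. Optionally, give the expected 95% CI half-width for home-based versus face-to-face: roughly ±0.63 SD with 20 per arm to ±0.78 SD with 14 per arm, at a correlation of 0.5.

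The cost is rewriting one paragraph. No participants, visits or analyses change, though the stated detectable effect becomes less favourable.

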#### Statistical Analysis

The analysis will be conducted using the ITT principle, including all randomized participants. Per-protocol sensitivity analyses will also be performed. For continuous variables, a linear mixed model will be used, with fixed effects for group (face-to-face, home-based, and control), time (baseline, postintervention, and follow-up), and group × time interactions. Participants will be modeled as a random effect. Baseline values will be included as part of the repeated-measures structure rather than as covariates, allowing the estimation of within- and between-group changes over time. Age and sex will be considered as covariates in adjusted models if baseline imbalances or clinically relevant associations with the outcomes are identified. The home-based vs face-to-face comparison will be interpreted based on effect estimates and confidence intervals and will not be treated as a formal equivalence analysis. This model, which treats repeated within-participant measures as a random effect, will be used. An appropriate covariance structure for the repeated measures will be selected based on model fit criteria. This method allows for the management of missing data under the assumption that they are missing at random. In cases of systematic losses, multiple imputations may be used as a complementary analysis.

For categorical or dichotomous variables, the chi-square or Fisher exact tests will be applied, where appropriate. For all hypothesis tests, the α level for statistical significance will be set at *P*<.0, corresponding to a 95% confidence level. To assess the magnitude of significant differences between the preintervention and postintervention moments and between groups, the Hedge *g* (x ®1–x ®2⁄ SD grouped) will be calculated. The effect size magnitudes will be interpreted as follows: <0.2, no effect; 0.2 to 0.4, small; 0.5 to 0.7, moderate; and ≥0.8, large [58]. Secondary outcomes will be analyzed using the same modeling strategy; however, these analyses will be considered exploratory, and no formal adjustment for multiple comparisons is planned. The data will be analyzed using IBM SPSS software, version 20.0, licensed to UDESC, and Microsoft Office Excel for Windows.

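### The primary mixed model is valid but gives up precision by leaving baseline means free in each randomized arm, and age and sex enter the adjusted models by a data-dependent rule

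*Protocol article*

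**What the plan says.** The Statistical Analysis section specifies a linear mixed model "with fixed effects for group (face-to-face, home-based, and control), time (baseline, postintervention, and follow-up), and group × time interactions", with participant as a random effect. On baseline it says: "Baseline values will be included as part of the repeated-measures structure rather than as covariates". The reason given is that this allows changes within and between groups to be estimated. No constraint on the baseline means is stated. The covariance form is left to the data: "An appropriate covariance structure for the repeated measures will be selected based on model fit criteria".

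On covariates the same section says: "Age and sex will be considered as covariates in adjusted models if baseline imbalances or clinically relevant associations with the outcomes are identified".

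Randomization and Blinding places the 1:1:1 allocation after the baseline assessment and says that the recruitment strata play no part in the randomization. Sample Size Calculation supplies the only correlation in the document, "with an assumed correlation among repeated measures of 0.50 and a nonsphericity correction (ε) of 1.0", and plans for 42 completers out of 60 recruited. The home-based versus face-to-face comparison is to be read from estimates and confidence intervals.

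**The concern.** Three groups by three times with a full interaction gives nine free means, three of them at baseline. With complete data and equal correlations, the group × time contrast is then a difference in change scores. Randomization makes the three true baseline means equal, so the model spends data on estimating differences known to be zero. In a trial of 60 people whose main comparison rests on interval width, precision that could be had for nothing is worth having.

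The covariate rule is a second, smaller issue. Baseline imbalance after randomization is chance, and an association with the outcome can be seen only by looking at outcome data. A covariate set chosen on either trigger makes the adjusted estimate depend on the data, and its nominal interval does not allow for the selection.

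**Working it through.** **The plan's own figure.** Inputs from Sample Size Calculation: "Considering an α level of .05 and power of .80", an effect size f "of 0.25 (moderate) was assumed for the group × time interaction", three groups, three times, ρ = 0.50 and ε = 1.0. The usual repeated-measures interaction formula has noncentrality λ = f² × N × m / (1 − ρ), with df₁ = (3 − 1)(m − 1) and df₂ = (N − 3)(m − 1).

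- N = 42, m = 3: λ = 0.0625 × 42 × 3 / 0.5 = 15.75, df 4 and 78, power 0.887.
- N = 36, m = 3: λ = 13.5, df 4 and 66, power 0.823. This is the smallest N with equal arms that reaches 0.80.
- N = 42, m = 2: λ = 10.5, power 0.803.

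So 42 does not follow from the stated inputs, which give 36. The gap is on the safe side and is a separate matter. The dropout step is right: 42 / 0.7 = 60. What follows uses only ρ, the 14 completers per arm (42 / 3) and the 20 recruited per arm (60 / 3).

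**Variance of a pairwise post-intervention contrast.** Assume equal variances σ² and a common correlation ρ, as ρ = 0.50 with ε = 1.0 implies. Let n_b per arm have a baseline value and n_p of them a post-intervention value.

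- Free baselines: 2σ² × [(1 − ρ²)/n_p + (1 − ρ)²/n_b]
- Common baseline: 2σ² × (1 − ρ²)/n_p

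With complete data (n_p = n_b = n) the free form reduces to 2σ² × 2(1 − ρ)/n, and the relative saving is (1 − ρ)/2.

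**Results at ρ = 0.50, in units of σ².** These agree with generalized least squares on the nine-mean and seven-mean models.

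| Data per arm | Free | Common | Saving |
|---|---|---|---|
| 14 complete | 2(0.75/14 + 0.25/14) = 0.1429 | 2(0.75/14) = 0.1071 | 25% |
| 20 at baseline, 6 lost before the post visit | 2(0.75/14 + 0.25/20) = 0.1321 | 2(0.75/14) = 0.1071 | 19% |
| 20 at baseline, 3 lost before post and 3 before follow-up | 2(0.75/17 + 0.25/20) = 0.1132 | 2(0.75/17) = 0.0882 | 22% |

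The standard error, and so the interval at a fixed critical value, shrinks by 1 − √0.75 = 13%, 1 − √0.811 = 10% and 1 − √0.779 = 12% respectively.

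**Difference detectable with 80% power** (normal approximation, 1.960 + 0.842 = 2.802 standard errors):

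- 14 complete: 1.06 SD falls to 0.92 SD.
- 6 lost before the post visit: 2.802 × 0.3635 = 1.02 SD falls to 2.802 × 0.3273 = 0.92 SD.
- 3 and 3 lost: 2.802 × 0.3365 = 0.94 SD falls to 2.802 × 0.2970 = 0.83 SD.

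**Sensitivity to ρ, post-intervention visit.**

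| ρ | Complete | 6 lost before post | 3 and 3 lost |
|---|---|---|---|
| 0.3 | 35% | 27% | 31% |
| 0.5 | 25% | 19% | 22% |
| 0.7 | 15% | 11% | 13% |

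**Covariates.** No arithmetic applies. Two covariates are named in advance, but whether they are used turns on what is observed at baseline or in the outcome.

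**The case against.** The planned model is unbiased under randomization, matches the interaction on which the trial was sized, and comes with a stated reason. A reader might infer that the plan contains an error, or that its primary result would be misleading. The documents do not support that: nothing is contradicted, and the point is one of efficiency. The stated reason does not require free baselines, however. A common-baseline model on the same three visits still estimates within-arm changes, and its joint test of arm effects at two post-baseline visits has (3 − 1) × 2 = 4 degrees of freedom, the same as the planned interaction.

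A reader might also take the quarter as what this trial will lose. That figure needs complete data and ρ = 0.50, which is a planning assumption. The plan keeps all randomized participants in the model, and under its own dropout the saving at the post visit is nearer a fifth.

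On covariates, a reader might infer that the primary model itself changes with observed imbalance. The text speaks of adjusted models and does not clearly put age and sex in the primary one. Only two covariates are in play, and Ethical Considerations has the statistician blinded until the primary analyses are complete, which limits deliberate steering. Thresholds and the choice of primary model may be settled in an analysis plan that is not shown, so their absence is not the complaint. What stands is that the rule as stated depends on the data.

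**Conclusion.** The point holds as a precision gain that needs only wording, not as a fault of validity. At ρ = 0.50 a common baseline mean lowers the variance of a pairwise post-intervention contrast by 25% with complete data and by about 19% to 22% with 30% dropout. Over ρ from 0.7 to 0.3 and the dropout patterns examined, the range is roughly 11% to 35%. These figures assume a common variance and correlation, treated as known, and data missing at random. The covariance structure finally selected could shift them.

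The conditional use of age and sex is a separate and lesser weakness. It makes the adjusted result data-dependent, and no size can be put on it from the document.

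A reader might suppose that entering baseline HADS as a covariate for the two later visits is the same remedy. It is not: that version drops anyone with no post-baseline visit, whereas the plan promises to analyse all randomized participants, and it does not directly give within-arm changes. Nor does the design call for adjustment for income or rural residence, which are recruitment quotas only.

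**What to change.** Keep the mixed model on all three visits, but replace the free baseline means by one mean common to the arms. The fixed effects become time and group × post-baseline time, with no group effect at baseline; in practice the arm indicators are set to zero at the baseline visit. All randomized participants stay in the model. Use the same form for the continuous secondary outcomes.

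Include age and sex in that model in advance, whatever imbalance or association is observed, and name it as the primary model.

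The cost is a change of wording before recruitment, scheduled for April 2026, plus two degrees of freedom for age and sex. No visit, measurement or participant is added.

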### Outcome Measures

#### Primary Outcome Measure

Assessments will be conducted before the start of the intervention, after the 7-week program, and at the 4-week follow-up (Figure 3). Data collection will be conducted in person at the UDESC facilities for both the face-to-face and home-based groups. In the initial assessment, a characterization questionnaire will be administered to obtain socioeconomic and health information (age, marital status, educational level, occupation, PA level, and main symptoms). Patient data will be maintained solely by the principal researcher to protect confidentiality throughout the study, from inception to conclusion. The variables analyzed, along with their respective instruments, are listed below.

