**Figure 3. F3:**
[figure not shown]
Schematic drawing of the in-person and home-based prehabilitation program protocol.

The primary outcome will be the total score of the Hospital Anxiety and Depression Scale (HADS). The HADS was developed in England [43] and was validated for Brazilian Portuguese by Botega et al [44]; the instrument showed internal consistency (Cronbach α) of 0.68 for anxiety and 0.77 for depression in its validation study. The instrument is a scale completed through an interview, preferably answered by the patient, and contains 14 questions, of which 7 assess anxiety (HADS-A) and 7 assess depressive symptoms (HADS-D). The scale emphasizes the psychological signs or consequences of anxiety and depression, excluding clinical symptoms such as dizziness and headache. The questions alternate, with half of them written in a positive tone and the other half in a negative tone. Each question is assigned a score from 0 to 3, with 3 indicating a state associated with more depressive symptoms or anxiety. Analyses of the HADS-A and HADS-D subscales will be conducted as secondary exploratory outcomes. In this study, HADS scores ≥8 will be used as a cutoff for each domain, as this is the score that indicates the presence of depressive and anxious symptoms and possible cases of depression and anxiety.

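### Choosing the covariance structure of the primary HADS model by fit can leave too simple a structure, and baseline-to-post contrasts may then exceed the 5% error rate if post-intervention and follow-up scores correlate more strongly than baseline and post scores

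*Protocol article*

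**What the plan says.** The Statistical Analysis section of the protocol article describes a linear mixed model with group, time and their interaction. Three of its sentences concern the within-person covariance:

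- The rule for choosing the structure: "An appropriate covariance structure for the repeated measures will be selected based on model fit criteria"
- The first mention of a random effect: "Participants will be modeled as a random effect"
- The second mention, later in the same paragraph: "This model, which treats repeated within-participant measures as a random effect, will be used"

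Baseline stays in the outcome vector: "Baseline values will be included as part of the repeated-measures structure rather than as covariates". The covariance therefore spans three visits. Their timing is given under Primary Outcome Measure: "Assessments will be conducted before the start of the intervention, after the 7-week program, and at the 4-week follow-up".

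The only covariance values in the article are in the Sample Size Calculation, "with an assumed correlation among repeated measures of 0.50 and a nonsphericity correction (ε) of 1.0". That section requires 42 participants and recruits 60 to allow for 30% dropout. Secondary outcomes use the same modelling strategy.

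**The concern.** Penalised fit criteria reward structures with few parameters. In a sample this small they can prefer a two-parameter structure even when it is wrong. The two obvious candidates share a restriction. Compound symmetry makes all three correlations equal. AR(1) treats the visits as equally spaced and makes the two adjacent correlations equal.

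The first interval is 7 weeks and contains the intervention; the second is 4 weeks and does not. It is plausible, though not documented, that post-intervention and follow-up scores are more alike than baseline and post-intervention scores. A restricted structure would then overstate the baseline-post correlation and understate the standard error of the change between those visits.

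At stake are the error rate and interval coverage of the pairwise HADS contrasts at post-intervention. Coverage matters because the home-based versus face-to-face comparison is to be read from estimates and confidence intervals.

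**Working it through.** **Inputs.** From the article: 3 arms, 1:1:1, 3 visits, 5% level, 60 recruited, 30% dropout, common correlation 0.50. Check: 60 × 0.70 = 42, or 14 per arm. Assumed: the other correlation patterns below, written baseline-post / post-follow-up / baseline-follow-up.

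**Parameter count.** Three visits have 3 variances and 3 covariances, so an unstructured matrix has 6 parameters. Compound symmetry and AR(1) have 2 each.

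**Large-sample check.** Take equal variances and complete data. With a full set of group-by-time means, the estimated contrast is the same under every structure; only its standard error changes. The variance of a baseline-to-post change is proportional to 2(1 − r), so

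SE ratio = √[(1 − r fitted) / (1 − r true)], and false-positive rate = 2[1 − Φ(1.96 × SE ratio)].

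Compound symmetry fits the mean of the three correlations. AR(1) fits the mean of the two adjacent ones. The true baseline-post correlation is 0.50 throughout.

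| True pattern | Structure | r fitted | SE ratio | False-positive rate |
|---|---|---|---|---|
| .5/.5/.5 (the plan) | either | 0.50 | 1.000 | 5.0% |
| .5/.7/.5 | compound symmetry | 1.70/3 = 0.567 | √(0.433/0.5) = 0.931 | 6.8% |
| .5/.7/.5 | AR(1) | 1.20/2 = 0.60 | √(0.40/0.5) = 0.894 | 8.0% |
| .5/.8/.45 | compound symmetry | 1.75/3 = 0.583 | √(0.417/0.5) = 0.913 | 7.4% |
| .5/.8/.45 | AR(1) | 1.30/2 = 0.65 | √(0.35/0.5) = 0.837 | 10.1% |

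The first row reproduces the plan's own position: no inflation. The others show the rate if the simple structure is always used.

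**Simulation with selection** (no treatment effect, REML, Satterthwaite degrees of freedom).

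*Wide candidate list:* compound symmetry and AR(1), each with equal or unequal variances; random intercept plus diagonal; random intercept plus AR(1); unstructured. Rates are for the post-intervention contrasts, with Monte Carlo error of about 0.3 to 0.5 points.

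| True pattern | Sample | AIC | BIC | Always unstructured |
|---|---|---|---|---|
| .5/.5/.5 | 20 per arm, 30% dropout | 5.9% | 6.0% | 5.6% |
| .5/.6/.5 | 14 per arm, complete | 6.0% | 6.5% | 5.0% |
| .5/.7/.5 | 14 per arm, complete | 6.5% | 7.6% | 5.1% |
| .5/.8/.45 | 20 per arm, 30% dropout | 6.8% | 9.4% | 5.4% |

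In the last row, fixing compound symmetry in advance gives 8.1% and fixing AR(1) gives 10.5%.

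*Short list (compound symmetry, AR(1), unstructured), 20 per arm, 30% dropout.* The baseline-post correlation was 0.50, baseline-follow-up 0.40 to 0.50 and post-follow-up 0.70 to 0.80. BIC chose AR(1) in 52 to 84% of trials and compound symmetry in 5 to 44%. Home-based versus control at post-intervention ran at 6.6 to 8.1% with BIC, 5.2 to 5.8% with AIC and 4.4 to 5.5% with unstructured always.

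*List that keeps the random effect (compound symmetry, random intercept plus AR(1), unstructured), same sample, five covariances.* The same contrast ran at 5.0 to 7.4% with BIC, 5.2 to 6.9% with AIC and 4.7 to 5.8% with unstructured always. The overall group-by-time test ran at 4.5 to 6.8%, 5.2 to 6.6% and 5.2 to 6.2% respectively.

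**Limit on the AIC figures.** They depend on the unstructured matrix being among the candidates. With AIC confined to random-intercept structures and unstructured left out, rates ranged from 4.5 to 8.5%.

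**The case against.** The strongest reply has four parts.

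1. **Fit-based selection is common, and the article is condensed.** The candidate list, criterion and fallback belong to an analysis plan that is not shown. This stands: their absence is not the point here. The point is the rule that the article does state.
2. **The inflation does not follow from the documents.** A reader might infer that the plan runs its primary contrasts at 8% or more. The article does not support that: its one covariance assumption gives about 5%, and the excess needs an assumed pattern and mainly a BIC-type criterion. Nor is the upper figure a ceiling, since it moves with the assumed correlations.
3. **The trial is sized on the group-by-time interaction, and that test is hardly touched.** This stands on the simulation above. The restricted structures understate some change variances and overstate others, so the errors partly offset. The concern is confined to the separate contrasts and their intervals.
4. **The analyst is blinded.** Ethical Considerations keeps group codes masked until the primary analyses are done. That makes steering difficult, but a blinded analyst still obtains the same understated standard error.

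Two further inferences should be resisted. Looking at the data is not itself the cause: a random intercept fixed in advance does about as badly. And the random effect does not make the model invalid. Combined with an unstructured residual it gives 7 parameters for a matrix that has 6, which is redundant, but the marginal covariance and the inference on the group means are unchanged. The article also does not say that the two will be combined.

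**Conclusion.** The point holds conditionally. If post-intervention and follow-up correlate more strongly than baseline and post, selection by fit in 42 to 60 participants gives a false-positive rate of about 5 to 9% for the baseline-to-post HADS contrasts: about 6 to 9% with BIC, and about 5 to 7% with AIC when unstructured is a candidate. Under the plan's own correlation of 0.50 and ε of 1.0, the rate stays near 5%. The cause is ending with too simple a structure. With only three visits the simpler structures save very little, so there is no good reason to accept the risk.

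**What to change.** Replace the selection sentence and the two random-effect sentences with:

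> Repeated measures will be modelled with an unstructured 3x3 covariance common to all arms, without a separate participant random effect, fitted by REML with Satterthwaite degrees of freedom.

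If a fallback for non-convergence is named, it should not force equal baseline-post and post-follow-up correlations without protection. Heterogeneous Toeplitz and compound symmetry both do so. Any simpler structure should be a last resort, used with robust (sandwich) standard errors and reported as such.

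**Cost.** Wording only; no change to data or participants. It should be settled before the analysis planned for October to November 2026. Under the plan's assumption, the mean standard errors with and without the unstructured matrix were 0.343 and 0.345, less than 1% apart. There is a small loss in degrees of freedom. With 42 complete cases they fall from (42 − 3) × 2 = 78 under compound symmetry to 42 − 3 = 39. The critical t value rises from 1.991 to 2.023, so intervals widen by about 1.6%.
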